## Abstract

**Background:**

Respiratory tract infections are an important burden in primary care and it’s known that they are usually self-limited and that antibiotics only alter its course slightly. This together with the alarming increase of bacterial resistance due to increased use of antimicrobials calls for a need to consider strategies to reduce their use. One of these strategies is the delayed prescription of antibiotics.

**Methods:**

Multicentric, parallel, randomised controlled trial comparing four antibiotic prescribing strategies in acute non-complicated respiratory tract infections. We will include acute pharyngitis, rhinosinusitis, acute bronchitis and acute exacerbation of chronic bronchitis or chronic obstructive pulmonary disease (mild to moderate). The therapeutic strategies compared are: immediate antibiotic treatment, no antibiotic treatment, and two delayed antibiotic prescribing (DAP) strategies with structured advice to use a course of antibiotics in case of worsening of symptoms or not improving (prescription given to patient or prescription left at the reception of the primary care centre 3 days after the first medical visit).

**Discussion:**

Delayed antibiotic prescription has been widely used in Anglo-Saxon countries, however, in Southern Europe there has been little research about this topic. The DAP trial wil evaluate two different delayed strategies in Spain for the main respiratory infections in primary care.

**Trial registration:**

This trial is registered with ClinicalTrials.gov, number http://NCT01363531.

## Background

Infectious diseases are among the most common complaints for family physicians. About 70% of these are respiratory tract infections, and the most common infections are acute bronchitis, pharyngitis and rhinitis [1]. Most of the respiratory tract infections are self-limiting, and according to recent systematic reviews, antibiotics have only a small effect on the course of most of these infections [2-10].

Besides, antibiotic treatment is no free of downsides including adverse events, increasing the costs for the same episode, and reinforcing beliefs about their usefulness. It has also been observed that antibiotic prescribing in respiratory tract infections correlates with a higher frequency of visits to the physician in the future, thus rising patients’ expectations about their use [11]. More importantly, though, the appearance and increase of bacterial antibiotic resistance is attributed mainly to the overuse of antibiotics [12]. This is a fundamental aspect since it may be increasingly more difficult to treat infections.

On the other hand, there is great variability in antibiotic prescribing among professionals, communities, and countries. Spain is one of the countries with the highest rate of antibiotic prescribing [13] and the rate of inappropriate antibiotic prescribing is also high, implying inappropriate use of resources [14,15].

Nevertheless, sometimes avoidance of antibiotic prescribing is still a challenge in patients with uncomplicated respiratory tract infections. Firstly, because it is not known which patients are at a higher risk of developing complications that, though uncommon, might be serious. Secondly, there are patients who wish and expect to be prescribed an antibiotic if symptoms do not subside [16], and physicians that overestimate the proportion of patients who expect be treated with antibiotics [17]. For these reasons, complete avoidance of antibiotic prescribing in patients with uncomplicated respiratory tract infections is not appropriate. 

Several studies have shown that the interventions aimed at reducing antibiotic prescribing may result in lower prevalence of resistant strains [12]. One of these interventions is the delayed prescription of antibiotics, in which the patient is prescribed an antibiotic that should be taken only in case of worsening of the symptoms or no improvement a few days after the visit. This strategy has been used in conditions where it may be difficult to differentiate between a viral and a bacterial etiology in primary care settings, such as respiratory tract infections and other infections such as conjunctivitis [18] or urinary tract infections [19].

A systematic review [20], concludes that delayed antibiotic prescription reduces antibiotic use without an increase in complications of these conditions, with little advantage compared with the non-prescription. This review shows how immediate compared to delayed antibiotic prescribing is associated with a consistently higher patient satisfaction. Additionally, other studies suggest that this strategy might reduce the number of visits [11,16] since patients can get rapid access to antibiotics in case of no improvement. Besides, as indicated by another systematic review [21] family doctors see this strategy as an intervention that may help them resolve uncertainties. Similarly, family doctors believe that reassures patients, providing them with control over their conditions and allowing them to reconcile with their expectations.

Despite the advantages seen in other parts of the world, no studies have evaluated the effectiveness and the acceptability of delayed prescription in Southern Europe. Only a single observational study [22] showed that this strategy might reduce antibiotic prescribing by 33%. For these reasons, we designed a multicenter, randomized clinical trial to assess delayed prescription in Spain.

The aim of this study is to establish the effectiveness of delayed antibiotic prescribing strategies versus antibiotic therapy and no therapy in terms of duration and severity of symptoms. Therefore, the study will establish the effectiveness of delayed antibiotic prescribing strategies versus antibiotic therapy and no therapy in terms of: antibiotic use at 30 days, satisfaction and belief in antibiotic effectiveness.

## Methods

Multicenter, randomized controlled clinical trial (Phase IV) comparing four therapy strategies for uncomplicated acute respiratory tract infections (clinicaltrials.gov, identifier NCT01363531).

### Randomization

Stratified by condition of interest (pharyngitis, rhinosinusitis, acute bronchitis, and exacerbations of chronic obstructive pulmonary disease). Centralized using a Web-based platform.

### Masking

Open-label study given the type of strategies used and given that an effect on their beliefs and the antibiotic use is expected.

### Experimental and control groups

Four treatment arms:

a) Group 1: immediate antibiotic therapy.

b) Group 2: no antibiotic therapy.

c) Group 3: delayed prescription by handing the prescription to the patient.

d) Group 4: delayed prescribing by collecting the prescription at the health care center from the third day after the initial visit.

The inclusion of no antibiotic and immediate antibiotic strategies is due to the need to evaluate their relative effectiveness compared with the delayed strategies. Potential differences among the delayed strategies are assessed by comparing the two delayed prescription strategies.

The choice of antibiotic therapy will depend on the specific respiratory tract condition and will be up to the physicians’ judgement, according to their usual clinical practice. Physicians will also handle symptomatic treatment and complications as needed.

### Inclusion and exclusion criteria

Patients over 18 years old with uncomplicated acute respiratory tract infections will be enrolled: acute pharyngitis, rhinosinusitis, acute bronchitis, and exacerbations of chronic bronchitis/mild to moderate chronic obstructive pulmonary disease. Patients with these infections will be included by the physicians as long as they are unsure of whether to use antibiotics or not. See details of the general and specific study criteria for each condition under [see Additional file 1].

### Study population and total number of patients

The sample size calculated is 600 patients. This is an estimate based on an average duration of 12 days (s.d. 6) for the main symptoms [16]. Considering a reduction of two days in the duration of the symptoms as a clinically relevant outcome, with a bilateral approximation, a sample of 600 patients will be able to detect this difference with an alpha error of 5% and a power of 80% (beta = 0.2). This estimate was calculated considering lower respiratory tract infections only. The project aims to be much broader (and therefore pragmatic, with an increase in the external validity at the conceptual phase), for this reason an exhaustive search will be carried out for all the conditions initially expected to be included (pharyngitis, rhinosinusitis, acute bronchitis, acute exacerbation of chronic bronchitis). The aim of this search is to obtain average values of the main endpoints defined in this project and to allow for standardization, and accordingly, a comparison (the variability that can be derived from the data obtained for the calculation has reached 50%, which indicates a high dispersion). It seems unlikely that the remaining conditions exceed that value, and generally, they will even tend to be lower. This allows avoiding the estimation of losses in the required total number of patients.

The patients will be equally distributed among the four evaluation groups to maximize power in the comparison. In addition, the four groups will be stratified in terms of the included conditions. Besides, focusing on the three groups except for the immediate antibiotic therapy, the 450 patients distributed in the three arms would allow to detect a difference of at least 13% in antibiotic use with the same indicated power (assuming that the figures for antibiotic use in the two delayed strategies are very similar: delayed strategy group 27% versus 14% in the group with no antibiotic therapy). Finally, in the comparison of four strategies for the variable *antibiotic use*, the study will have a 100% for antibiotic use as an outcome, since the percentage of antibiotic use in the antibiotic therapy arm is likely to exceed 90%. For the calculations we used Sample Power Release 2.0 software.

Criteria for withdrawals and expected analysis of withdrawals and dropouts:

•Serious adverse event

•Unsatisfactory therapeutic effect

•Patient clinical conditions prevent compliance with the protocol

•Protocol violation

•Informed consent withdrawal

Patients can choose to interrupt the medication any time during the course of the study. However, they will be followed up in the same way as the other patients. Analyses will follow the intention-to-treat principle, with patients being analysed in the groups to which they were randomized.

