### Data analysis

In order to ensure their similarities, a baseline comparison of the treatment groups will be performed. If any clinically relevant differences are found, a multivariate analysis will also be performed to ensure the absence of biases resulting from them. Differences will be deemed significant if p < 0.05. The SPSS software version 21.0 will be used for the calculations.

The comparisons among the treatment groups will be as follows: The differences for categorical variables will be described using contingency tables (and the corresponding percentages); inferencing will be made by means of an exact Fisher test or Chi-square test. The Kruskall-Wallis test will be used for ordinal or quantitative variables with heteroscedasticity or abnormality issues. In case of significance, the decision on the groups will be based on the 2 × 2 Mann–Whitney test; no corrections will be applied for multiple comparisons, calculated the means and the higher and lower values for each group. For quantitative variables, the analysis of variance (ANOVA) test will be used, resorting to post-hoc in case of significance, thus showing the means and the standard deviations for each group.

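### The stated 80% power for a two-day difference fits one ungated pairwise comparison; under the planned omnibus-first rule, power for a specified pair is about 63–81% with normal data

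*Protocol article*

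**What the plan says.** Under Study population and total number of patients, the article states: "The sample size calculated is 600 patients". The inputs are "an average duration of 12 days (s.d. 6) for the main symptoms", a two-day target ("Considering a reduction of two days in the duration of the symptoms as a clinically relevant outcome") and a two-sided approach ("with a bilateral approximation"). It concludes that "a sample of 600 patients will be able to detect this difference with an alpha error of 5% and a power of 80" per cent. Allocation is equal: "The patients will be equally distributed among the four evaluation groups to maximize power in the comparison". That gives 600 / 4 = 150 per arm, with no addition for losses. The section names the software used but no test, no pair of arms and no set of four means.

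Under Data analysis, the procedure for quantitative variables has two steps. On the parametric route, "the analysis of variance (ANOVA) test will be used, resorting to post-hoc in case of significance"; the post-hoc test is not named. On the rank route, used where variances are unequal or normality fails, a Kruskal–Wallis test comes first: "In case of significance, the decision on the groups will be based on the" pairwise Mann–Whitney test, left unadjusted for multiplicity. The significance level is 0.05.

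**The concern.** The two sections do not visibly describe the same procedure. The sample-size section speaks of detecting one two-day difference. The analysis section makes any claim about a pair conditional on a test across all four arms. A pair is declared different only if both steps succeed, so the power for that pair cannot exceed the power of either step, and it depends on where the other two arms lie. A power figure for such a rule needs an assumed pattern of four means, and none is given.

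Duration of symptoms is part of the main endpoint, and the questions posed are largely pairwise: delayed strategies against immediate treatment, against no treatment, and against each other. A reader of a null result would take 80% as the chance that a true two-day difference between two named strategies would have been found. If that chance is nearer two in three, the null result carries less weight than the article suggests.

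**Working it through.** **Inputs from the article.** SD 6; difference 2 days; two-sided alpha 0.05; 150 per arm; no losses.

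**Step 1: reproduce the stated figure as one pairwise comparison.**
- Normal approximation: n per arm = 2 × (1.960 + 0.842)² × (6/2)² ≈ 141.3, so 142, or 568 in four arms. The exact t-test needs 143 per arm, or 572.
- Power at 150 per arm: standard error = 6 × √(2/150) = 0.693; 2/0.693 = 2.887; Φ(2.887 − 1.960) = 82.3%. The exact t-test gives 82.1%.
- Mann–Whitney with normal data (relative efficiency 0.955): 142/0.955 = 148.7, so 149 per arm, or 596 in total. Simulated power at 150 per arm is about 80%.

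The 600 and the 80% are therefore reproduced closely by a single pairwise test.

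**Step 2: power of the four-group ANOVA alone.** Noncentrality λ = n × Σ(μᵢ − μ̄)² / SD², with 3 and 596 degrees of freedom. The patterns are assumptions; each contains at least one two-day pair.

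| Arm means (assumed) | Σ(μᵢ − μ̄)² | λ = 150 × Σ / 36 | ANOVA power |
|---|---|---|---|
| 12, 11, 11, 10 | 2.00 | 8.33 | 67.1% |
| 12, 11.33, 10.67, 10 | 2.22 | 9.26 | 72.2% |
| 12, 12, 11, 10 | 2.75 | 11.46 | 81.9% |
| 12, 12, 12, 10 | 3.00 | 12.50 | 85.4% |
| 12, 12, 10, 10 | 4.00 | 16.67 | 94.2% |

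**Step 3: power of the whole rule for one specified two-day pair (four-group test significant and pair significant).** Simulation with normal data, SD 6, 150 per arm and unadjusted follow-up. ANOVA used 400,000 replicates (standard error about 0.1 point). Kruskal–Wallis used 4,000 (√(0.63 × 0.37 / 4,000) ≈ 0.8 point).

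| Arm means (assumed) | ANOVA, then pair | Kruskal–Wallis, then Mann–Whitney |
|---|---|---|
| 12, 11, 11, 10 | 65.8% | 62.6% |
| 12, 11.33, 10.67, 10 | 69.4% | not run |
| 12, 12, 11, 10 | 75.2% | not run |
| 12, 12, 12, 10 | 77.1% | 74.5% |
| 12, 12, 10, 10 | 80.8% | 78.7% |

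On the ANOVA route the gap from 80% is 14.2 points in the first row and 2.9 points when one arm differs; it vanishes when two arms differ from two. In the first row the omnibus test is the bottleneck: 67.1% pass it, and almost all of those (65.8%) also show the pair.

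**Step 4: sensitivity to skewness, rank route.** The order is both midway, one arm different, two against two. Gamma-distributed durations with SD 6 in every arm give about 79%, 88% and 90%. Gamma durations with coefficient of variation 0.5 give about 69%, 80% and 83%. The range is therefore about 70–90%.

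**The case against.** The strongest case against has four parts.

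1. **The origin of the 80% is not documented.** No test is named. A reader might infer that the figure came from a two-arm t-test and that the omnibus step was overlooked. The article does not establish this. A two-arm Mann–Whitney lands nearer to 600 (596 against 572), and a four-arm ANOVA with means 12, 12, 11, 10 needs 144 per arm (576) and has 81.9% at 150, as close as the t-test. This stands: one can say only what the figure is consistent with.

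2. **Success need not mean one named pair.** The omnibus test alone has 82–94% power in three of the five patterns, and the power to find at least one two-day pair is 81.4%, 85.4% and 94.3% in those three. This also stands. A reader might conclude that the stated power is simply false; that is too absolute, since it depends on a definition of success and a pattern of means that the article leaves open.

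3. **Normality.** The rank route is reserved for data that fail the ANOVA assumptions, so the low figures from normal data under Kruskal–Wallis describe a case that the plan would mostly send to ANOVA. This stands as a caveat, and the skewed-data figures show the effect. It does not touch the ANOVA results.

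4. **Pairwise justification is a common simplification, and this is a condensed article.** That bears on how serious the matter is. But the gate and the 80% are both printed in the article, so the missing link is not merely detail left to an unseen analysis plan.

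A figure for a Bonferroni-corrected pair would be out of place, because no such correction is planned. The ANOVA post-hoc test is unnamed; if it were Tukey, power for the pair would be about 60–62%.

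**Conclusion.** The point holds in a limited form. The stated 80% is right for one pairwise comparison of 150 against 150. It is not shown for the omnibus-first rule in the Data analysis section, where power for a specified two-day pair is about 63–81%. In four of the five patterns examined with ANOVA and normal data, it falls below 80%.

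These figures rest on normal data, SD 6, 150 analysed patients in every arm, unadjusted follow-up tests, success defined as a specified pair, and patterns of means that are not in the article. No pattern can be called the expected one on the article's evidence, so the "two in three" reading applies only if both other arms lie midway. Nor do the documents support the inference that 600 is miscalculated or that the trial needs more patients. What needs correcting is an unqualified power statement that does not match the written decision rule.

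**What to change.** In the sample-size section, name the pair of strategies compared, the test and the assumed four means. Then do one of two things:

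- replace the unqualified 80% with the power of the omnibus-first rule under those means, for example about 77% by ANOVA if one arm differs from three equal arms, or about 66% if the other two arms lie midway; or
- state that 80% refers to a single ungated pairwise test, and that the planned rule may have less power for a given pair.

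Dropping the omnibus step would be a design choice and is not required. The cost is one paragraph and, under the first option, a less favourable stated figure in most patterns. The 600 patients, the allocation and the data collected stay as they are.

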### Enrollment

Enrollment will be carried out competitively at the participating physicians’ clinics and is expected to take one year. The study will be carried out in five Spanish Autonomous Communities (Catalonia, Galicia, Basque Country, Navarre and Madrid).

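### The 80% power was derived for lower respiratory tract infections and carries over to the four-condition mix only under unstated conditions, while the planned tests leave out condition, the randomisation stratum

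*Protocol article*

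**What the plan says.** All references are to the protocol article, Methods.

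- **Study population and total number of patients.** "The sample size calculated is 600 patients". The inputs follow: "This is an estimate based on an average duration of 12 days (s.d. 6) for the main symptoms", a 2-day target ("Considering a reduction of two days in the duration of the symptoms as a clinically relevant outcome"), a two-sided test ("with a bilateral approximation") and "with an alpha error of 5% and a power of 80% (beta = 0.2"). The four arms are equal, so 150 per arm. The section then discloses the source population: "This estimate was calculated considering lower respiratory tract infections only".
- **Same section, the bridge to the wider population.** A literature search for all conditions is planned. The dispersion used is already 50%, and the remaining conditions are thought unlikely to exceed it. No mean, SD or expected share is given for any other condition. The same reasoning is used to add no allowance for losses.
- **Inclusion and exclusion criteria.** "Patients over 18 years old with uncomplicated acute respiratory tract infections will be enrolled: acute pharyngitis, rhinosinusitis, acute bronchitis", together with exacerbations of chronic bronchitis or mild to moderate COPD.
- **Enrollment.** "Enrollment will be carried out competitively at the participating physicians’ clinics". No quota per condition is stated.
- **Randomization.** Stratified by the four conditions.
- **Data analysis.** ANOVA, or Kruskal-Wallis followed by Mann-Whitney. Multivariate analysis is planned only if clinically relevant baseline differences are found.

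**The concern.** A power statement holds for the population whose mean, spread and target went into it. Here those inputs describe two of the four eligible conditions. The bridging argument speaks only to relative spread (SD divided by mean) and leaves two things open.

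1. **Between-condition variance.** If conditions differ in typical duration, pooling them adds variance that has nothing to do with treatment. A relative spread of 50% within each condition does not bound it. The tests named in Data analysis do not remove it. The multivariate step is unlikely to be triggered by condition, because stratified randomisation should balance condition across arms.
2. **The effect.** Two days is one sixth of a 12-day illness and one third of a 6-day illness. The article does not say whether the same absolute gain is expected in the shorter illnesses.

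Duration is part of the main endpoint. Readers of the pooled result need to know what effect the enrolled mix could detect, and the article gives them a flat 80%.

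**Working it through.** **Inputs from the article:** mean 12 days, SD 6 (6/12 = 50%), difference 2 days, two-sided 5%, power 80%, 150 per arm.

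**Inputs assumed, because the article gives none:** lower-tract share s = 25%, 50% or 75%; upper-tract mean m = 5, 6, 8 or 10 days; SD equal to 50% of the mean in every condition. The two lower-tract conditions are treated as one group with mean 12, and the two upper-tract conditions as one group with mean m.

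**Step 1. The plan's own figure.** n per arm = 2(1.960 + 0.842)² × 6² / 2² = 141.3, so 142 per arm and 568 in total. Dividing by the Mann-Whitney efficiency of 0.955 gives 149 per arm, 596 in total. At 150 per arm, pairwise power is 82%. So 600 is sound for lower-tract infection and slightly generous by the plain formula.

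**Step 2. Variance in the mix.**

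- Within conditions: W = 36s + (1 − s)(m/2)²
- Between conditions: B = s(1 − s)(12 − m)²
- An unadjusted comparison uses SD = √(W + B). One adjusted for condition uses √W.
- Power ≈ Φ(difference / (SD × √(2/150)) − 1.96).

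Example with s = 50%, m = 6: W = 18 + 4.5 = 22.5 and B = 0.25 × 36 = 9. The unadjusted SD is √31.5 = 5.61 and the adjusted SD is √22.5 = 4.74.

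**Step 3. Two readings of the effect**, 150 v 150:

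- *Common effect:* 2 days in every condition.
- *Proportional effect:* one sixth of each condition's mean, so the pooled difference is (12s + (1 − s)m)/6. In the example this is 9/6 = 1.5 days.

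| s = 50% | SD unadj. / adj. | Common 2 days: power unadj. / adj. | Proportional: difference | Proportional: power unadj. / adj. |
|---|---|---|---|---|
| m = 5 | 5.78 / 4.60 | 85% / 96% | 1.42 | 56% / 76% |
| m = 6 | 5.61 / 4.74 | 87% / 95% | 1.50 | 64% / 78% |
| m = 8 | 5.48 / 5.10 | 89% / 92% | 1.67 | 75% / 81% |
| m = 10 | 5.61 / 5.52 | 87% / 88% | 1.83 | 81% / 82% |

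**Step 4. Full assumed range** (s = 25–75%, m = 5–10):

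- Common 2 days, unadjusted: SD 4.74 to 6.14, power about 80% to 95%.
- Proportional, unadjusted: power about 53% to 81%.
- Proportional, adjusted for condition: power about 75% to 82%.

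**Step 5. If the spread assumption fails.** With an upper-tract SD of 75% of the mean and a common 2-day effect, unadjusted power is about 67% to 90%.

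**The case against.** **The limitation is disclosed and argued.** This is true. The article names the restriction, gives a reason for carrying the number over and plans a search. But the reason covers relative spread only, and the article reports no search result.

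**Under the article's own target, the 80% survives.** Also true. With an absolute 2-day effect and a relative spread of 50%, pooled power is about 80–95% over the assumed range, because shorter illnesses bring smaller SDs. The 53–81% appears only when a proportional effect is substituted. Nothing in the article says that relevance scales with illness length, and an absolute difference in days is a legitimate threshold. So the documents do not support a claim that the trial is underpowered.

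**Stronger readings a reader might reach, and why they fail:**

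- *The power describes a population that the trial will not enrol.* Acute bronchitis and exacerbations of chronic bronchitis or COPD are two of the four conditions. The calculated population is part of the enrolled one.
- *Power among lower-tract patients alone is too low.* At a 50% share it would be about 53%, but the article promises no 80% within that subset.
- *The target should become a ratio of durations.* That is one defensible choice. Nothing in the article requires it.

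**A condensed article may leave detail to a full protocol or analysis plan.** Agreed for values per condition. But this article does state its comparisons, and as stated they take no account of the randomisation stratum.

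**Conclusion.** The point holds in a limited form. The 600 patients and 80% are correct for lower-tract infection. For the mix that will be enrolled, the 80% depends on two conditions: a common 2-day effect in all four conditions, and a relative spread of at most 50% in each. The second is asserted without figures and the first is not stated at all. If both hold, power is about 80–95%. If the effect is proportional instead, it is about 53–81% unadjusted, and adjustment for condition recovers most of the loss (75–82%). The documents do not show which case applies, so the direction of any error is unknown.

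The clearer weakness is in the analysis. Leaving condition out of the duration comparison costs power under either reading whenever mean durations differ. With half the patients upper tract and a mean of 5, 6 or 8 days, a common 2-day effect has 85–89% power unadjusted and 92–96% adjusted.

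These figures rest on assumed upper-tract means and shares, on grouping four conditions into two, on normal-theory power, and on a single pairwise comparison with all 150 patients per arm analysed.

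**What to change.** 1. **Data analysis.** State that symptom duration will be compared between arms stratified by or adjusted for condition, the randomisation stratum. Examples are ANOVA with condition as a factor, or a stratified rank test where normality or equal variance is doubtful. This should be planned from the start and not depend on finding baseline differences.
2. **Study population and total number of patients.** State that the 80% was computed for lower-tract infection (12 days, SD 6), and that it carries over to the four-condition mix only if a common 2-day effect and a relative spread of at most 50% hold in every condition.

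The cost is a sentence or two in each section and one factor in the analysis. The power statement becomes conditional where it is now flat. No extra patients, no ratio scale and no power claim for any single condition are needed.
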